### Measurements

#### Assessments

Baseline assessment will be completed prior to pre-enrollment into the ramp-up period (Fig. 3). Additional follow-up assessments will be completed at 6 weeks after enrollment into the study and 12 weeks at completion of the study. Assessment at baseline will include demographic characteristics, vital signs and physical exam, and the following questionnaires: Patient Reported Outcomes Measurement Information System (PROMIS-29 v 2.0) to measure health-related quality of life^30^ (HrQoL), Godin-Shephard Leisure Time Physical Activity Index (LTPA)^31^ and Duke Activity Status Index (DASI)^32^ to measure self-reported physical activity, the Patient Activation Measure (PAM^®^)^33^ to measure patient activation, and DietID^™^
^34^ and the Automated Self-Administered Dietary Assessment Tool (ASA24)^35^ to measure dietary patterns. PROMIS-29 v2.0 is an NIH-supported HrQoL measure of 29 questions that cover broad domains including physical function, anxiety, depression, fatigue, sleep disturbance, participation in social roles and activities, and pain intensity with built-in normative references to the US general population.^30^ The LTPA is a 3-question survey that measures how much strenuous, moderate, and mild exercise a person completes in a 7-day period. A weekly leisure-time activity score is calculated to categorize a patient’s activity level.^31^ The DASI is a validated 12-question survey designed to estimate a patient’s functional capacity.^32^ The Patient Activation Measure is a 13-item survey to measure a patient’s knowledge, skill and confidence in managing one’s own health and healthcare. Patients are categorized into 4 levels: Disengaged and overwhelmed, becoming aware but still struggling, taking action and gaining control, and maintaining behaviors and pushing further.^33^ DietID^™^ uses the patented Diet Quality Photo Navigation (DPQN^®^), which uses pattern recognition instead of dietary recall or food logs to provide a dietary assessment.^34^ Patients are presented composite images of established dietary patterns and are asked to select images most like their own, current food intake until a best fit is achieved. Outputs include the Healthy Eating Index (HEI-2020) and nutrient analysis. The ASA24 is a self-administered 24-hr recall dietary assessment developed by the National Cancer Institute.^35^

LFI: liver frailty index, LTPA: Godin-Shephard Leisure Time Physical Activity Index, PROMIS-29 v2.0: Patient Reported Outcomes Measurement Information System, DASI: Duke Activity Status Index, BIA: Bioimpedance analysis, ASA24: Automated self-administered 24-hour Dietary Assessment, PAM^®^: Patient Activation Measure

#### Body composition

Body composition will be measured using bioimpedance analysis (Quantum VII Biological Impedance Analyzer from RJL Systems) including fat, fat-free mass, lean dry mass, total body water, intra-cellular water, bone mineral content, lean soft tissue, skeletal muscle mass, phase angle, fat mass index, and fat free mass index. Anthropometric measurements including waist circumference, hip circumference, waist to hip ratio, waist to height ratio, midarm muscle circumference, and triceps skin fold will also be measured.

#### Laboratory data

Laboratory results to measure safety will be conducted at baseline, 6 weeks in the study, and 12 weeks in the study. Laboratory values to be obtained include liver function tests (AST, ALT, ALP, Total bilirubin) and kidney function (creatinine, eGFR, BUN, cystatin C).

### STRIVE Digital Health Program

STRIVE is a semi-supervised nutrition and exercise program delivered through the Heal-Me digital health application. Designed to improve frailty among older adults with cirrhosis, the program is structured into three pillars: Exercise, Nutrition, and Life Skills. The 12-week program includes home-based pre-recorded programs to be completed three times per week for 30 minutes. The mild-to-moderate intensity exercise program consists of functional, resistance, 30-second to 2-minute aerobic intervals, and stretch training. Patients are provided Therabands of varying difficulty to facilitate participation in home exercise videos. The nutrition and life skills pillars include videos, reading materials, interactive surveys, and life skills videos and surveys including developing readiness for change, SMART goals, self-compassion, sleep habits, and managing habits. Patients also have regular weekly check-ins with the clinical research coordinator, exercise specialist or physician and biweekly check-ins with a nutritionist to optimize patient’s engagement in study and provide personalized recommendations.

### Creatine/whey protein and placebo supplementation

Creatinine/whey protein and non-sugar based placebo powder supplementation will be provided at a dosage of 5g creatine and 35g whey protein daily or one daily serving of placebo powder respectively given 30 minutes prior to exercise on exercise days and anytime on days without exercise.^36^ This dose was determined based on general doses of creatine and/or whey protein supplementation provided in other studies among athletes and older adults.^27, 37^ Kidney and liver function will be evaluated at baseline, 6 weeks, and 12 weeks. Participants who develop a ≥ 5 times increase from baseline or upper limit of normal of AST/ALT, ≥ 1.5 times increase of creatinine, or any grade 3–4 laboratory abnormality will be evaluated for dose reduction or discontinuation. If patients experience moderate gastrointestinal symptoms interfering with daily activities, persistent muscle cramps, or ≥ 5 pound weight gain over 1 week with concern for fluid retention, participants will initially undergo reduction of supplementation to half dose at week 1 week and re-escalation to full dose at week 2 if symptoms resolve. If symptoms persist at half dose, supplementation is discontinued and patients will continue STRIVE digital health programming.

### Study Outcomes

The primary outcome will be physical frailty using LFI, a validated, cirrhosis-specific frailty measure consisting of grip strength, chair stands, and balance testing.^38^ We have previously found that a change in LFI of 0.3 units is associated with improved survival.^39^ We therefore define a change in LFI of at least 0.3 units during the course of the 12-week program as clinically significant in this study. Secondary outcomes will include change in HrQoL by PROMIS-29 v2.0, physical activity by DASI, healthy eating index by dietary pattern, and body composition by BIA and morphologic measures.

### Sample size

We aim to randomize 200 total participants (100 per arm) for this study. Calculations were performed using PASS sample size software and were based on two-sample t-test assuming equal variances with a significance-level of α = 0.05, testing the difference between two means, e.g., change in LFI between start of study and study completion between participants randomized to creatine/whey protein supplementation vs. placebo. Based on published cohorts that report a mean LFI of 3.8 (SD 0.72–0.77) in similar populations,^40^ the common standard deviation for both groups is assumed to be 0.75. The proposed sample size is powered at 80% to detect a mean change in LFI in the creatine/whey supplementation group that is 0.3 LFI-units greater than the mean change in LFI in the placebo group. We have previously found that a change in LFI of 0.3 units is associated with improved survival.^39^

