**Methods:**

This study is a randomized, placebo-controlled trial including older adults (≥ 60 years) with cirrhosis evaluated at a single health center. We will recruit 200 patients informed by sample size calculations. Patients will be randomized 1:1, stratified by Child Pugh Class and gender. Participants who meet eligibility criteria will be automatically enrolled in a 2-week “ramp-up” period to assess engagement in the exercise portion of STRIVE prior to full enrollment into the 12-week study (STRIVE with creatine/whey protein supplementation vs placebo). We will assess health-related quality of life using Patient Reported Outcomes Measurement Information System (PROMIS-29 v 2.0), self-reported physical activity using Duke Activity Status Index (DASI), patient activation using Patient Activation Measure (PAM^®^), and diet quality by healthy eating index using DietID^®^ and Automated Self-Administered Dietary Assessment Tool (ASA24). Body composition scan (BIA), liver frailty index (LFI), and morphologic measurements including waist circumference, hip circumference, midarm muscle circumference, and triceps skin fold will be measured. The primary outcome will be physical frailty (by LFI); secondary outcomes will include health-related quality of life (HrQoL), physical activity, healthy eating index, and body composition.

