## Methods/Design

### Study design and setting

We will conduct a prospective double-blind placebo-controlled, two-arm randomized controlled trial at a single center (Fig. 1). To ensure patients in the study are able to navigate the STRIVE platform and perform exercises on STRIVE, all eligible patients will first be pre-enrolled in a two-week “ramp-up” period during which they will participate in a simplified version of the digital health program that includes weekly exercise videos, post-video surveys, and weekly telehealth check-ins with a physician and/or exercise specialist to monitor their weekly exercise and adjust exercise prescriptions as needed. Patients who achieve ≥ 80% engagement with app activities and scheduled check-ins during the ramp-up period will proceed to randomization. Patients enrolled in the study will be randomized to creatine/whey protein supplementation vs placebo supplementation and STRIVE digital health programming. The STRIVE digital health programming uses the same interface as the ramp-up but includes three pillars: exercise, nutrition, and life skills (Fig. 2). Activities in the app include pre-recorded exercise videos to be completed three times per week, educational videos and reading, and interactive quizzes and surveys. Patients also receive weekly physician or exercise specialist check-ins to monitor exercise progression and to recommend personalized modifications; weekly check-ins with clinical research coordinator for safety monitoring, app-related questions, and supplement adherence evaluation; and biweekly check-ins with a nutritionist to assess dietary habits and provide personalized dietary recommendations. Patients are evaluated in-person at baseline prior to the ramp-up period, at 6 weeks after enrollment into STRIVE, and at 12 weeks at completion of STRIVE.

LFI: liver frailty index, PAR-Q: Physical Activity Readiness Questionnaire for Everyone, PROMIS-29 v2.0: Patient Reported Outcomes Measurement Information System, DASI: Duke Activity Status Index, BIA: Bioimpedance analysis

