## Discussion

Older adults with cirrhosis represent a population of patients highly vulnerable to both age- and cirrhosis-related causes of frailty. Additionally, frailty is associated with accelerated clinical decompensation and death. Frailty therefore represents an attractive target to improve clinical outcomes, HrQoL, and healthcare expenditure.^8^

Chronic liver disease creates a catabolic state that drives the development of muscle dysfunction among adults with cirrhosis.^8^ Exercise and mobile-assisted exercise strategies have shown improvements in muscle health among adults with cirrhosis. A feasibility study of exercise and nutrition programming delivered on an earlier version of the Heal-Me digital application showed 70% engagement rates with an 89% satisfaction rate among 23 adults with cirrhosis with Child Pugh Class A and B cirrhosis.^43, 44^ Other home-based exercise programming among adults with cirrhosis have shown improvements in muscle-related factors including sarcopenia and physical frailty.^19^

Protein-energy malnutrition due to impaired nutrient intake, altered metabolism, and chronic inflammation, is another important pathway leading to frailty and sarcopenia among adults with cirrhosis.^8^ Nutrition prehabilitation with increased protein intake or supplementation have similarly shown improvements in frailty among adults with cirrhosis. In a randomized control trial of adults with compensated cirrhosis, 54 patients were enrolled to receive 16-week supplementation with branched-chain amino acids vs placebo twice daily. Patients on BCAA supplementation showed higher rates of frailty reversal (36% vs 0%, p < 0.001), significantly increased skeletal muscle index by BIA (7.5 vs 7.8, p = 0.03), and improved quality of life.^28^

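### The stated 80% power holds at the plan's SD of 0.75 only if all 200 randomised participants have a week-12 LFI; there is no allowance for attrition

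*Protocol article*

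**What the plan says.** The Sample size section fixes the number at randomisation: "We aim to randomize 200 total participants (100 per arm) for this study". The calculation is a "two-sample t-test assuming equal variances with a significance-level of α = 0.05". The target is a mean change in the supplement arm "that is 0.3 LFI-units greater than the mean change in LFI in the placebo group", and "the common standard deviation for both groups is assumed to be 0.75", a value taken from published cohorts with LFI SDs of 0.72 to 0.77. The conclusion is worded as a property of the randomised number: "The proposed sample size is powered at 80% to detect a mean change in LFI in the creatine/whey supplementation group". The section gives no missing-data rate and no inflation.

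The Statistical analysis section analyses all randomised participants on the change in LFI from the beginning of the study to completion. The model has terms for arm, Child Pugh score and gender, and none for baseline LFI.

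The abstract words the number differently: "We will recruit 200 patients informed by sample size calculations". Under Study design and setting, only patients who reach at least 80% "engagement with app activities and scheduled check-ins during the ramp-up period will proceed to randomization".

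**The concern.** A sample size given as the number randomised normally carries a margin for participants who are not measured at the primary time point. Here the margin appears to be nil.

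The LFI combines grip strength, chair stands and balance, and the final visit is in person at 12 weeks. Eligible patients are at least 60 years old, have an LFI of 3.8 or more, and may be in Child Pugh class C. The Background describes older adults with cirrhosis as especially vulnerable, and the abstract's Discussion includes patients on the transplant waitlist. Death, transplant, decompensation or withdrawal could each leave no week-12 LFI, and a participant without one has no change score for the primary model as described.

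At stake is the headline power claim for the primary outcome. If it is overstated, the trial has a greater chance than stated of missing an effect of 0.3, the size the protocol itself defines as clinically significant. The missing margin does not in itself affect type I error or bias the estimate.

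**Working it through.** **Inputs, all from the Sample size section.** Difference 0.3; common SD 0.75; alpha 0.05; power 80%; 100 per arm. Sidedness is not stated. By the normal approximation a two-sided test needs 99 per arm and a one-sided test 78, so only the two-sided test matches the plan's number.

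**Step 1: reproduce the plan's figure.** The standardised difference is 0.3 / 0.75 = 0.4.

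- Normal approximation: n per arm = 2 × (1.960 + 0.842)² / 0.4² = 98.1, rounded up to 99.
- Exact two-sample t-test (noncentral t): n per arm = 99.08, rounded up to 100, so 200 in total.
- Power of the t-test at 100 per arm: 80.4%.

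The figure of 200 reproduces with zero loss. The margin is 100 − 99.08 = 0.92, less than one participant per arm. Had loss been built into these inputs, the stated total would exceed 200.

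**Step 2: power when some week-12 values are missing.** Evaluable n per arm = 100 × (1 − d), with the SD held at 0.75. The article gives no rate, so d is an assumption shown over a range. The detectable difference is the value that gives 80% power at that n.

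| Missing (assumed) | Evaluable per arm | Power for 0.3 | Difference detectable with 80% power |
|---|---|---|---|
| 0% | 100 | 80.4% | 0.299 |
| 5% | 95 | 78.3% | 0.306 |
| 10% | 90 | 76.1% | 0.315 |
| 15% | 85 | 73.7% | 0.324 |
| 20% | 80 | 71.0% | 0.334 |

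**Step 3: how far this depends on the SD.** The 0.75 is the spread of LFI at one time point, but the outcome is a change. With equal variances at both visits and correlation r between them, SD of change = 0.75 × √(2(1 − r)). The article gives no r, so these values are assumptions too.

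| r (assumed) | SD of change | Power, 100 per arm | Power, 80 per arm |
|---|---|---|---|
| 0.4 | 0.82 | 72.9% | 63.1% |
| 0.5 | 0.75 | 80.4% | 71.0% |
| 0.6 | 0.67 | 88.2% | 80.3% |
| 0.7 | 0.58 | 95.3% | 90.1% |

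Using 0.75 for the change therefore amounts to assuming r = 0.5. Above that there is unstated slack; below it, power is short even with complete data.

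Varying the SD directly over the cited range gives 92 per arm needed at 0.72 (power 83.4% at 100 per arm) and 105 needed at 0.77 (power 78.3% at 100 per arm).

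**The case against.** The strongest counter-argument concerns the SD. If baseline and week-12 LFI correlate at 0.6 or more, 80 per arm still reaches 80%, so a loss of 20% would do no harm. Eligibility at LFI 3.8 or above, which is the mean of the cited cohorts, also narrows the baseline spread and could lower the SD of change further. This stands as a limit on the point: it would be wrong to say that the trial must miss its power as soon as one LFI is missing. It does not remove the point, because the protocol states no correlation and makes no such argument, and at r = 0.4 the same uncertainty works against it.

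It is also fair that the ramp-up selects engaged patients, that participants must be able to stay at least 3 months, and that those who stop the supplement for persistent symptoms continue the programme. All of this may keep loss low. It cannot be counted on to make loss zero, and zero is what the calculation needs at SD 0.75.

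A reader might go further and infer from the abstract that 200 is the intake to the ramp-up, so that the engagement gate leaves far fewer randomised. The documents do not support this. The Sample size section says explicitly that 200 will be randomised, and the design, eligibility and randomisation sections all place randomisation after the gate. Nor can the Discussion's feasibility result ("showed 70% engagement rates with an 89% satisfaction rate among 23 adults with cirrhosis") serve as a pass rate: it describes engagement with an earlier version of the app, not the share of patients who clear an 80% threshold. No power loss from the ramp-up can be derived from this document.

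**Conclusion.** The point holds, conditionally. Under the plan's own inputs, 80% power belongs to 200 participants measured at week 12, yet the text attributes it to 200 randomised. With the SD held at 0.75, an assumed 10% to 20% missing lowers power by about 4 to 9 percentage points (80.4% to 76.1% or 71.0%). The detectable difference then rises to between 0.315 and 0.334, above the protocol's clinically significant 0.3.

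This rests on three things: a two-sided test, which the plan's number implies; an SD of change of 0.75, which the plan assumes but does not justify for a change score; and the missing rates, which are mine. Actual power could lie on either side of these figures, depending on the unstated correlation.

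The abstract's wording on recruitment is loose and should be aligned, but it does not change the design. Overall this should be fixed, but it is a correction to a stated figure and not a flaw that blocks the trial.

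**What to change.** 1. In the Sample size section, state that 200 randomised participants give 80% power only with complete week-12 LFI and an SD of change of 0.75. Name the test as two-sided.
2. Add power and detectable difference at plausible missing rates, for example the 10%, 15% and 20% rows above.
3. Claim 80% power under attrition only if a stated, sourced baseline to week-12 correlation supports it, with baseline LFI as a covariate in the primary model. As an illustration under the same equal-variance assumption, the residual SD is then about 0.75 × √(1 − r²). At an assumed r = 0.5 this is 0.65, and 80 per arm gives 82.7%. At an assumed r = 0.3 it is 0.72, and 90 per arm gives 79.9%.
4. In the abstract, change recruit to randomize so that it matches the Sample size section.

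The cost is a text change. No patients are added. The stated power becomes slightly less favourable unless item 3 is adopted, and item 3 must be settled before any outcome data are seen by arm.

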### Data collection, validation, and management

Data will be collected and inputted into REDCap database. A clinical research coordinator will control data input before locking files within this study.

### Safety Management

An independent Data and Safety Monitoring Board will monitor interim data as the study progresses to ensure participant safety and review efficacy. The board will include two transplant hepatologists independent of the study and will review data, evaluate emerging safety information, adjudicate adverse event relatedness, patient discontinuation decisions, and other issues. Serious adverse events will be reviews monthly by the board.

### Statistical analysis

Analyses will be evaluated in the intention-to-treat population (all randomized participants). For the primary analysis, change in frailty (LFI) between the beginning of the study and study completion will be calculated for all participants, and the mean change will be modeled using a linear regression model that includes terms for trial arm (creatine/whey protein supplementation vs. placebo) and variables used in the randomization procedure (Child Pugh score and gender).^41, 42^Continuous secondary outcomes will be analyzed in the same way. In addition, changes in frail status (LFI ≥ 4.4) between the beginning of the study and study completion will be modeled using a logistic mixed effects regression model that includes fixed effects for trial arm and variables used in the randomization procedure and random effects for each participant to account for the within-participant correlation.

Exploratory models may adjust for prognostic variables and/or baseline variables that exhibit imbalance due to chance[cite]. Additional as-treated or per protocol analyses may be performed.

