### Randomization

Patients who meet eligibility criteria and complete the two-week ramp-up period will be randomized using a 1:1 allocation ratio to placebo vs creatine/whey protein supplementation and permuted blocks of sizes of lengths 2 and 4 by the statistician. Randomization will be stratified by Child Pugh score (A, B, C) and gender (women, men). Six randomization lists will be generated by the study biostatistician using R “randotools” package for each combination of stratification factors: A/female, B/female, C/female, A/male, B/male, C/male. The randomization list will be used to assign eligible and consented participants to one of the two trial arms of the study to the pharmacy. Patients will receive a blinded box of creatine/whey protein vs placebo in single daily sachets with instructions on use.

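### Adding baseline LFI to the primary model would be a free gain in precision; the planned change-score analysis is valid without it

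*Protocol article*

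**What the plan says.** The Statistical analysis section of the protocol article defines the primary endpoint as a difference from baseline: "change in frailty (LFI) between the beginning of the study and study completion will be calculated for all participants". It models this with a "linear regression model that includes terms for trial arm (creatine/whey protein supplementation vs. placebo) and variables used in the randomization procedure", and names those variables as Child Pugh score and gender. It then extends the model: "Continuous secondary outcomes will be analyzed in the same way".

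The Randomization section confirms that LFI is not a stratification factor: "Randomization will be stratified by Child Pugh score (A, B, C) and gender (women, men"). No listed term therefore carries baseline LFI directly.

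The one other route for baseline variables is in the same Statistical analysis section: "Exploratory models may adjust for prognostic variables and/or baseline variables that exhibit imbalance due to chance".

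The Sample size section plans for 100 per arm using a "two-sample t-test assuming equal variances with a significance-level of α = 0.05", and "the common standard deviation for both groups is assumed to be 0.75". It makes no allowance for baseline adjustment.

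**The concern.** Subtracting the baseline does not remove its influence. If LFI has the same SD at both visits and correlation rho between them, the slope of week-12 LFI on baseline is rho, so the slope of change on baseline is −(1 − rho). Unless rho is 1, participants who start frailer tend to show a larger fall in LFI whichever arm they are in.

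Two things follow when baseline LFI is left out:

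- Variation in change that baseline could explain stays in the residual, so the standard error is larger than it need be.
- If one arm happens to start frailer, its mean change looks better by about (1 − rho) times the baseline difference, and the primary model has no term to correct this.

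The article states the model terms outright, so this is not a detail left open for a separate analysis plan. If an imbalance did occur, the trial would have an unadjusted primary result and perhaps an adjusted exploratory one, with no stated rule on how to weigh them.

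**Working it through.** **Inputs from the protocol article.** 100 per arm, target difference 0.3, SD 0.75, α = 0.05 (Sample size). Published LFI mean 3.8 with SD 0.72–0.77 (Sample size). Entry at LFI ≥ 3.8 (Inclusion Criteria).

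**Assumptions, not in the document.** A two-sided test. Baseline-to-week-12 correlation rho of 0.3, 0.5, 0.7 or 0.9. LFI bivariate normal with mean 3.8 and SD 0.75 at both visits before the entry cut-off is applied. No loss to follow-up.

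**Step 1: the plan's own figure.** The standard error of the difference is 0.75 × √(2/100) = 0.106. The exact two-sided t-test (198 df) for a difference of 0.3 has power 80.4%, and 100 per arm is the smallest size reaching 80%. The stated calculation reproduces.

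**Step 2: without the entry cut-off.** The variance of change is 2 × 0.75² × (1 − rho). The variance adjusted for baseline is 0.75² × (1 − rho²). Their ratio is (1 + rho)/2, or 0.65, 0.75, 0.85 and 0.95 at the four values of rho. At rho 0.5 the SD of change is 0.75, and the adjusted SD is 0.75 × √0.75 = 0.650. Power would then rise from 80.4% to 90.1%.

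**Step 3: with the entry cut-off.** A normal distribution cut at its mean has variance 0.75² × (1 − 2/π) = 0.2044, so the baseline SD is 0.452. Selection on baseline leaves the regression slope and residual variance unchanged, so:

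- change-score variance = (1 − rho)² × 0.2044 + 0.5625 × (1 − rho²)
- adjusted variance = 0.5625 × (1 − rho²)

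Power is for a difference of 0.3 at 100 per arm (198 df for change, 196 df adjusted):

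| rho | SD, change | SD, adjusted | Variance ratio | Power, change | Power, adjusted |
|---|---|---|---|---|---|
| 0.3 | 0.782 | 0.715 | 0.84 | 77.0% | 83.9% |
| 0.5 | 0.688 | 0.650 | 0.89 | 86.6% | 90.1% |
| 0.7 | 0.553 | 0.536 | 0.94 | 96.9% | 97.6% |
| 0.9 | 0.330 | 0.327 | 0.98 | >99.9% | >99.9% |

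For example, at rho 0.5: 0.25 × 0.2044 + 0.4219 = 0.4730, and 0.4219 / 0.4730 = 0.89.

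**Step 4: shift from a chance imbalance.** The standard error of the baseline difference is 0.452 × √(2/100) = 0.064.

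- An imbalance of 1.96 standard errors is 0.125 units. It shifts the change-score estimate by 0.5 × 0.125 = 0.063 at rho 0.5 and 0.3 × 0.125 = 0.038 at rho 0.7, which is 21% and 13% of the 0.3 target.
- The median absolute imbalance is 0.6745 × 0.064 = 0.043 units. It shifts the estimate by 0.022 and 0.013, which is 7% and 4% of the target.

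**The case against.** The case for leaving the plan alone has several parts.

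- **The analysis is valid.** Under 1:1 randomization the change score and the baseline-adjusted model estimate the same treatment effect. The change score is unbiased over randomization, type I error is kept, and the stated power reproduces. This stands in full.
- **The gain may be small.** A reader might infer from Step 2 that adjustment lifts power from 80% to 90%. The document does not support that. It ignores the entry criterion, which narrows the baseline spread, and it takes rho 0.5 only because that value makes the SD of change equal 0.75. With the cut-off the gain is 3.5 points at rho 0.5 and under 1 point at 0.7. It reaches about 7 points only at rho 0.3. Child Pugh class and gender may already absorb part of it.
- **The imbalance is not a second defect.** The change-score standard error already includes this variation, so the shift in Step 4 is the same precision loss seen after the fact. A 1.96-standard-error imbalance is a tail case, exceeded about 5% of the time. This stands.
- **Regression to the mean is not a bias here.** Selecting on LFI ≥ 3.8 could suggest that the treatment comparison is distorted. Regression to the mean is expected equally in both arms and cancels in the difference.
- **Baseline LFI may not be the strongest predictor of change.** That would be a reasonable expectation, but nothing in the document establishes it, and the point does not need it.
- **Exploratory adjustment is allowed.** This helps but does not settle the matter: it is optional, may depend on the imbalance observed, and lies outside the primary estimate.
- **The full protocol or analysis plan may say more.** It may, but the article lists the model terms explicitly, and baseline LFI is not among them.

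**Conclusion.** The point holds as a recommended improvement in precision, not as an error that invalidates the primary analysis. Under the stated assumptions, leaving out baseline LFI costs about 16% of the variance at rho 0.3, 11% at 0.5, 6% at 0.7 and 2% at 0.9. The power cost at 100 per arm runs from about 7 percentage points at rho 0.3 to nothing visible at 0.9. Adjustment would also remove the dependence of the estimate on a chance difference in baseline LFI.

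The size rests on rho, which the document does not give, and on a normal LFI distribution with mean 3.8 and SD 0.75 cut off at 3.8. The direction does not depend on a particular value: under this model, any rho below 1 gives a lower adjusted variance. The same reasoning applies to the continuous secondary outcomes, but the document gives no figures from which to size the loss there.

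**What to change.** In the Statistical analysis section, prespecify the primary model as week-12 LFI, or change in LFI, on trial arm, baseline LFI (continuous), Child Pugh class and gender. Once baseline LFI is a covariate, the two forms of outcome give the same treatment effect, so the estimand and the 0.3-unit target are unchanged. Use the same baseline value that enters the change score. Add the corresponding baseline value to the model for each continuous secondary outcome.

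The cost is a change of wording in the protocol or analysis plan. Baseline LFI is already measured to establish eligibility, so no visits, participants or data are added, and the sample size need not change. The covariate should be fixed before unblinding, so that it cannot look like a choice made on the results.
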